## 3. Ethics and Dissemination

### 3.1. Ethical Approval and Consent to Participate

The study protocol has been reviewed and approved by the Ethics Committee for Research of the University of Salamanca (approval code: 1424). The trial will be conducted in strict accordance with the ethical principles of the Declaration of Helsinki [64]. Prior to enrollment, all eligible participants will receive detailed verbal and written information regarding the study’s objectives, procedures, potential risks, and benefits. Written informed consent will be obtained from all subjects before any study-related procedures are performed. Participation is strictly voluntary, and no financial compensation will be provided. Participants reserve the right to withdraw from the study at any time without any negative consequences for their usual care.

### 3.2. Confidentiality and Data Management

All data collected during the study will be recorded systematically, confidentially, and in an encoded manner. To ensure anonymity, each participant will be assigned a unique alphanumeric identification code. Personal identifying information will not be included in the analysis database. Data protection and privacy will comply with the General Data Protection Regulation (EU) 2016/679 [65] and the Spanish Organic Law 3/2018 on the Protection of Personal Data and Guarantee of Digital Rights [66]. The principal investigator will securely store the correspondence list between the codes and personal identities in a separate, encrypted file, accessible only to authorized research team members.

### 3.3. Dissemination Policy

Upon completion of the study, the global aggregated results will be shared in annual community scientific dissemination events. Additionally, participants will have the option to request a personalized report detailing their individual progress and outcomes regarding mobility, muscle strength, body composition, and pain-related variables throughout the trial. The clinical and scientific findings derived from this protocol will be submitted for publication in peer-reviewed medical journals and presented at national and international scientific conferences.

## 4. Results

As this manuscript represents a study protocol, there are no results to report at this stage. Participant recruitment and data collection are scheduled to be carried out as outlined in the study timeline. Upon completion of the trial, the collected data will be analyzed using the statistical methods described above to evaluate both the intra- and intergroup efficacy of the interventions. The final results will be disseminated through peer-reviewed scientific publications and presentations at national and international conferences.

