### 2.2. Participants and Eligibility Criteria

The study population will consist of community-dwelling older adults aged 65 years or older (Salamanca, Spain), recruited through the “Programa de Revitalización Geriátrica (PReGe)”. Inclusion criteria are as follows: (1) age ≥65 years; (2) history of primary chronic musculoskeletal pain lasting more than 3 months; (3) pain intensity ≥3 out of 10 on the Numeric Rating Scale (NRS) [44,45]. Exclusion criteria are as follows: (1) presence of secondary chronic pain conditions (e.g., oncological pain, specific rheumatic diseases such as ankylosing spondylitis or rheumatoid arthritis, fibromyalgia, neuralgias, and nerve injuries or neuropathies such as carpal tunnel syndrome); (2) severe psychiatric pathologies; (3) uncontrolled systemic, inflammatory, or cardiac diseases; or (4) other medical conditions that contraindicate physical exercise.

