### 2.3. Randomization and Blinding

Following the baseline assessment, eligible participants will be randomly assigned to one of the three study groups using a computer-generated sequence (R software version 4.2.1; R Foundation for Statistical Computing, Vienna, Austria), utilizing a block randomization design to ensure balance between the groups. Allocation will be performed by an independent researcher uninvolved in the recruitment process. Due to the nature of the intervention (exercise and education), it is not possible to blind the participants or the therapists. However, a single-blind design will be employed: the evaluators in charge of recording the outcome variables will be unaware of the group allocation, and the statistical analysis will be performed by an independent researcher using coded data, ensuring they also remain completely blinded to the group distribution and allocation.

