### 2.5. Outcomes and Data Collection

Evaluations will be conducted at three time points: Baseline (T0), Intermediate at 8 weeks (T1), and Final at 32 weeks (T2).

Primary Outcome: The primary outcome will be pain intensity measured by the NRS [32,33].Secondary Outcomes: Psychosocial variables will include Kinesiophobia (Tampa Scale for Kinesiophobia, TSK-11) [50,51], Pain Catastrophizing (Pain Catastrophizing Scale, PCS) [52], chronic pain grade and related disability (Chronic Pain Grade Scale) [53], and health-related quality of life (SF-12) [54,55]. Physical performance will be evaluated using the Short Physical Performance Battery (SPPB) [56], the Timed Up and Go (TUG) test [57], handgrip strength (JAMAR Plus+ dynamometer; Performance Health, Warrenville, IL, USA) [58], and the force–velocity profile of the lower extremities (ADR linear encoder; ADR Inercial, Toledo, Spain) [59]. Changes in body composition (Tanita BC-418 Bioelectrical Impedance; Tanita Corporation, Tokyo, Japan) [60,61] and daily analgesic consumption will also be recorded. Additionally, adherence to the intervention will be rigorously monitored by recording participant attendance at all multicomponent exercise and Pain Neuroscience Education sessions. Finally, the Trail Making Test (TMT) will be administered at baseline to evaluate executive function and cognitive flexibility [62,63]. The inclusion of this instrument is based on an a priori secondary hypothesis that baseline levels of these capacities modulate the responsiveness to PNE, given that this educational intervention requires high cognitive flexibility to successfully reconceptualize the pain experience [22,26].

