### 2.6. Sample Size and Statistical Analysis

The sample size was calculated based on the primary outcome (pain intensity via NRS). The estimation was performed using the GRANMO Version 8.0 tool. We calculated the effect size based on a Minimal Clinically Important Difference (MCID) of 1.5 points and a common standard deviation of 1.8. Assuming a two-sided contrast and an Analysis of Variance (ANOVA) for three independent groups, with an alpha level of 0.05, a statistical power of 80%, and an anticipated dropout rate of 10%, a minimum of 30 participants per group is required, resulting in a total sample of 90 subjects.

Intention-to-treat analysis will be performed. The primary endpoint for determining the long-term efficacy of the interventions is defined as the change in the primary outcome (NRS) at 32 weeks. Mixed-effects models for repeated measures will be used to evaluate intra- and intergroup changes over time (T0, T1, T2), considering the Group × Time interaction. To adjust for initial variance, baseline values of each respective outcome will be included as covariates in all models. Within this modeling framework, missing data will be inherently handled using restricted maximum likelihood (REML) estimation under the missing-at-random assumption. Additionally, to control for the inflation of Type I error associated with the analysis of multiple secondary outcomes, the Benjamini–Hochberg False Discovery Rate procedure will be applied. Furthermore, a secondary analysis stratified by sex will be conducted to evaluate potential differences in the intervention’s efficacy between men and women. Additionally, baseline TMT scores will be utilized as a covariate in an a priori secondary analysis to determine if baseline levels of executive function and cognitive flexibility modulate the treatment outcomes. The significance level will be set at *p* < 0.05.

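### Within-arm change in NRS is to be read as efficacy, although entry is selected on the same scale and no arm is untreated

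*Protocol article*

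**What the plan says.** Section 2.2 makes "pain intensity ≥3 out of 10 on the Numeric Rating Scale (NRS") an entry condition. Section 2.5 uses the same scale for the outcome: "The primary outcome will be pain intensity measured by the NRS". Under section 2.6 the primary endpoint "is defined as the change in the primary outcome (NRS) at 32 weeks".

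On timing, section 2.3 says "Following the baseline assessment, eligible participants will be randomly assigned". Section 2.5 lists ratings at T0, T1 and T2, and no separate screening rating is described. Section 2.4 and Table 1 give the same exercise programme to every arm, and section 2.4 calls the control group an active comparator.

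On analysis, section 2.6 says "Mixed-effects models for repeated measures will be used to evaluate intra- and intergroup changes over time", and the Abstract uses the same pairing. Both speak of changes. Section 4 goes further and says the analysis will "evaluate both the intra- and intergroup efficacy of the interventions". The article nowhere says that the within-arm part is descriptive.

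**The concern.** A one-sided entry threshold on a noisy score admits people who happened to rate high that day and excludes people who happened to rate low. On re-rating, the mean of those admitted falls even if nothing was done. Chronic pain also has its own course over 32 weeks. With no untreated arm, the trial cannot separate either component from a treatment effect within an arm.

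If within-arm change is reported as efficacy, a fall under exercise alone could be credited to exercise when part of it comes from selection. The wording also leaves room for the argument that one arm works because its T0-to-T2 change is significant and another does not because its change is not. That is no substitute for testing the difference between arms.

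**Working it through.** The article gives no figure for regression to the mean, so there is none to reproduce. The check asks how large the fall could be with no treatment effect.

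**Inputs from the article**
- Entry cut: NRS of at least 3 (section 2.2).
- Completers per arm: 30 × (1 − 0.10) = 27 (section 2.6).
- Common SD 1.8 and MCID 1.5 points (section 2.6).

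**Assumptions not in the article**
- Source population mean 3.5 to 6, SD 1.8 to 2.2, test-retest reliability r 0.6 to 0.8.
- The qualifying rating is T0 itself.

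**Formula.** For a normal score selected at cut c, expected fall = (1 − r) × SD × λ, where λ = φ(a) / (1 − Φ(a)) and a = (c − mean) / SD. On an integer scale, a cut of 3 corresponds to about 2.5 on the underlying continuous score.

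**Worked example** (mean 5, SD 2.2, cut 2.5)
- a = (2.5 − 5) / 2.2 = −1.136.
- λ = 0.2092 / 0.8721 = 0.240.
- At r = 0.6: 0.4 × 2.2 × 0.240 = 0.21 points.
- At r = 0.8: 0.2 × 2.2 × 0.240 = 0.11 points.

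**Simulation.** True score plus error, rounded to 0–10, entry at 3 or more, retest from the same true score, and a two-sided paired t-test at 5% in an arm of 27. Each cell gives r = 0.6, then r = 0.8.

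| Source mean | Source SD | SD after selection | Mean fall | Rejection per arm |
|---|---|---|---|---|
| 3.5 | 2.2 | 1.51 | 0.48; 0.26 | 25%; 15% |
| 4.5 | 1.8 | 1.47 | 0.19; 0.10 | 9%; 7% |
| 5 | 2.2 | 1.78 | 0.22; 0.11 | 9%; 7% |
| 5.5 | 2.2 | 1.85 | 0.16; 0.08 | 7%; 6% |
| 6 | 1.8 | 1.68 | 0.05; 0.03 | 5%; 5% |

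Over the full assumed range the fall is about 0.03 to 0.5 points and rejection about 5% to 25%. If the article's 1.8 is read as the baseline spread of those enrolled, the third and fourth rows match it best: a fall of about 0.1 to 0.2 points and 6% to 9% rejection.

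**Between-arm check.** With no effect, source mean 4, SD 2.2, r = 0.6 and 27 per arm, the baseline-adjusted F test across the three arms rejected in 5.1% of 4000 simulated trials. Randomisation spreads the regression equally over the arms, so the contrast keeps its nominal error.

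**The case against.** The strongest reply is that the point rests on one word in a placeholder section. Section 4 reports no results and defers to the methods already described, and section 2.6 and the Abstract speak only of changes. Estimating within-arm change from a repeated-measures model is routine. The hypotheses in section 5 are comparative (PNE plus exercise against exercise alone, and 32 weeks against 8 weeks), and none concerns an arm's own change. All of this stands and keeps the point small. It does not make the word efficacy in section 4 correct, because nothing in the article limits the within-arm analysis to description.

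A second reply is that the mechanism is partly inferred. The article does not say that the qualifying NRS is the T0 rating, and a condensed article may leave the screening procedure to the full protocol. If eligibility is rated earlier, some regression happens before T0 and the artefact shrinks. This also stands. Natural course would still have no control within an arm.

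A third reply is that baseline is a covariate in all models. That protects the between-arm contrasts, but it does not remove the average fall from a within-arm change.

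A reader might infer more than the document supports:
- *The primary comparison is biased.* It is not, as the 5.1% shows.
- *The trial already claims within-arm efficacy.* It plans to evaluate it, and no claim has been made.
- *Most trials of this kind would show a falsely effective arm.* The chance of at least one significant arm in three does reach about 57% under unfavourable assumptions, but three independent 5% tests give 1 − 0.95³ = 14% with no regression at all. With rejection of 6% to 9% per arm it is about 17% to 24%. The high figure needs a source mean close to the cut, which nothing in the article indicates.

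**Conclusion.** The point holds in a limited form. A within-arm fall in NRS from T0 cannot be read as efficacy in this design, and section 4 plans to read it so. That conclusion follows from the entry rule, the shared scale and the absence of an untreated arm, and does not depend on the simulation.

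The size does depend on assumptions. Across the stated range the artefact is about 0.03 to 0.5 NRS points, with 5% to 25% rejection per arm. In the settings closest to the article's SD of 1.8 it is about 0.1 to 0.2 points, with 6% to 9% rejection. Even the upper end, 0.5 points, is a third of the 1.5-point MCID. The rejection rates are for a simple paired test, whereas the article plans a mixed model, so they indicate scale only. The randomised contrasts, and with them the trial's main answer, are not affected.

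**What to change.** In section 4, replace intra- and intergroup efficacy with between-group efficacy. In the Abstract and section 2.6, state that within-arm changes are descriptive (estimate with 95% confidence interval) and that all efficacy conclusions rest on the randomised between-group contrasts.

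This is wording only and needs no added participants, visits or measurements. The one cost is that the sponsor gives up within-arm efficacy claims, which the design cannot support.

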## 5. Discussion

As populations age, an increasing number of older adults suffer from chronic musculoskeletal pain, a condition that often cannot be effectively managed exclusively through pharmacological treatments or under a traditional biomedical model. There is an urgent need to develop and implement non-pharmacological interventions based on empirical evidence [16,17,18]. To maximize their utility, these interventions must be designed in a way that allows them to be applied by health professionals in different settings (such as primary care centers or community spaces), thereby facilitating older adults’ access to pain management services and promoting self-management in their daily lives.

The present multicomponent intervention has been designed in accordance with these principles, integrating physical training and PNE based on current clinical recommendations. By combining both strategies, this study seeks not only to improve physical functionality but also to equip patients with cognitive tools to modify maladaptive thoughts and behaviors, such as kinesiophobia and catastrophizing, which often perpetuate disability in this population [10,11,12,13]. The protocol will be evaluated through a randomized controlled trial that introduces an innovative approach: comparing the effects of two different doses of education (8 weeks versus a 32-week maintenance phase) combined with exercise, against isolated exercise practice.

Based on this design, our primary hypothesis is that the combined intervention (PNE and exercise) will yield superior improvements in pain intensity, physical functionality, and psychosocial variables (such as kinesiophobia and catastrophizing) compared to exercise alone. Furthermore, we hypothesize that the extended 32-week PNE program will be significantly more effective in sustaining these clinical benefits and behavioral changes over time than the 8-week program. In addition to these clinical outcomes, we introduce an a priori secondary hypothesis regarding the moderating role of baseline cognitive flexibility and executive function, measured via the TMT. Chronic pain, particularly in older adults, often impairs these cognitive capacities [67,68,69]. Concurrently, PNE strictly requires pain reconceptualization, a process of unlearning deeply ingrained biomedical beliefs to adopt a biopsychosocial paradigm that inherently demands both of these cognitive functions [24,26]. Therefore, we propose that the baseline levels of executive function and cognitive flexibility will dictate the patient’s capacity to assimilate the educational intervention.

In the context of current literature, our protocol directly addresses several gaps identified in recent research. While recent meta-analyses and trials confirm that combining PNE with exercise yields significant clinical benefits in diverse populations, including older adults [28,36,37], most existing studies are limited by short intervention periods and a lack of long-term follow-ups. Furthermore, there is considerable heterogeneity regarding the optimal educational dosage. A recent dose–response meta-analysis established a threshold of 150 to 200 min of PNE to achieve clinically meaningful changes in pain and disability [42]. Our 8-week intensive phase (240 min) is specifically designed to safely exceed this threshold. However, considering the deep-rooted nature of maladaptive biomedical beliefs in older adults, short-term interventions might be insufficient to sustain behavioral changes. By introducing the 32-week maintenance arm, this trial expands upon current publications to explore whether sustained engagement and periodic reinforcement are required to consolidate pain reconceptualization and maintain active coping strategies over time.

From a methodological perspective, the design ensures that all participants in the three study arms benefit from a structured physical training program of the same duration and intensity. This guarantees an equivalent level of exposure to exercise, which will allow a rigorous and isolated evaluation of the true efficacy of PNE and its long-term dose–response effect. The study presents limitations inherent to non-pharmacological clinical trials, primarily the impossibility of applying double blinding (neither the participants nor the physiotherapist delivering the education can be blinded). However, this bias will be mitigated through a single-blind design, in which the evaluators in charge of data collection and the researchers performing the statistical analysis will be completely unaware of the group allocation.

## 6. Conclusions

This study protocol outlines a rigorous randomized controlled trial designed to address a critical gap in the management of geriatric chronic pain by evaluating the long-term dose–response effect of PNE combined with multicomponent exercise. By prioritizing active coping strategies over traditional passive treatments, this trial provides an innovative approach specifically tailored to the neurocognitive and physical needs of older adults. If our hypotheses are confirmed, the findings will generate high-quality evidence to determine the optimal educational dosage required for sustained pain relief. Ultimately, this will support the integration of combined active interventions into community settings, representing a safe and low-cost alternative centered on patient empowerment, promoting active aging, and reducing the burden of chronic pain in our communities.

## 7. Trial Registration

This trial protocol was prospectively registered at ClinicalTrials.gov (National Library of Medicine, USA) under the identifier: NCT07287501.

## Figures and Tables

**Figure 1 jcm-15-03696-f001:**
[figure not shown]
CONSORT flow diagram of the study protocol outlining the enrollment, allocation, follow-up, and planned analysis of participants. CG: Control Group; IG1: Intervention Group 1; IG2: Intervention Group 2; PNE: Pain Neuroscience Education; T1: Evaluation at 8 weeks; T2: Evaluation at 32 weeks.

**Table 1 jcm-15-03696-t001:** Description of the intervention protocols for the three study groups.

Feature	Control Group	Intervention Group 1 (IG1)	Intervention Group 2 (IG2)
Intervention Type	Multicomponent Exercise	Exercise + PNE (Short term)	Exercise + PNE (Long term)
Total Duration	32 weeks	32 weeks	32 weeks
Exercise Protocol	Frequency: 3×/week Duration: 50 min/session Content: Aerobic, Strength, Balance, Flexibility.	Frequency: 3×/week Duration: 50 min/session Content: Aerobic, Strength, Balance, Flexibility.	Frequency: 3×/week Duration: 50 min/session Content: Aerobic, Strength, Balance, Flexibility.
PNE Protocol	None	Duration: 8 weeks Frequency: 2×/week Total Dose: 240 min (16 sessions)	Duration: 32 weeks Phase 1: 8 weeks (2×/week) Phase 2: Weeks 9–32 (1×/2 weeks) Total Dose: 360 min (24 sessions)

**Table 2 jcm-15-03696-t002:** Structure, content, and objectives of the multicomponent exercise sessions.

Phase	Duration	Content	Objectives and Exercises
Warm-up	15 min	Active static and dynamic mobility	Objective: To prepare the musculoskeletal and cardiovascular systems. Exercises: Joint mobility and low-intensity movements during gait.
Main Phase	30–35 min	Aerobic, strength, and balance/coordination	Objective: To improve cardiovascular endurance, muscle power, and prevent falls. Exercises: Walking/marching, upper/lower limb resistance training, and dual-task balance challenges with cognitive stimuli (e.g., numbers, colors).
Cool-down	10 min	Stretching and breathing	Objective: To promote physical recovery and relaxation. Exercises: Static stretching of major muscle groups and guided diaphragmatic breathing.

**Table 3 jcm-15-03696-t003:** Content of the Pain Neuroscience Education (PNE) sessions.

Phase	Group	Session	Content and Pedagogical Objective
Phase 1: Intensive Educational Program (Weeks 1–8)	IG1 & IG2	Session 1	Presentation of the intervention, study objectives, and individual expectations. To establish a therapeutic alliance and align expectations.
Phase 1	IG1 & IG2	Session 2	Pain, perception, and context: Subjectivity of pain and the influence of environmental factors. To understand that pain is a subjective experience modulated by context.
Phase 1	IG1 & IG2	Session 3	Neurotag and sensory homunculus: How past memories and experiences affect pain. To recognize how past experiences and brain representation influence pain.
Phase 1	IG1 & IG2	Session 4	Acute pain vs. long-lasting pain: Protective function versus loss of protection (faulty alarm metaphor). To differentiate between the protective function of acute pain and the “faulty alarm” of chronic pain.
Phase 1	IG1 & IG2	Session 5	Peripheral and central sensitization: Understanding hypersensitivity and pain without a justified cause. To understand nervous system hypersensitivity without linking it to tissue damage.
Phase 1	IG1 & IG2	Session 6	Difference between damage and pain: Having pain does not necessarily mean there is a tissue injury. To decouple the concept of pain from structural injury.
Phase 1	IG1 & IG2	Session 7	Delivery of educational leaflet 1, knowledge verification questionnaire, and review of doubts. To consolidate theoretical knowledge and resolve doubts.
Phase 1	IG1 & IG2	Session 8	Introduction to active pain coping: Brainstorming tools to improve long-lasting pain. To transition from passive to active self-management tools.
Phase 1	IG1 & IG2	Session 9	Impact of chronic pain in older adults: Prevalence and the biopsychosocial complexity of pain. To validate the patient’s experience and introduce the biopsychosocial model.
Phase 1	IG1 & IG2	Session 10	Options for improvement: Limitations of imaging tests and drugs; importance of healthy daily habits (sleep, diet, social relations). To emphasize the role of lifestyle habits over passive medical interventions.
Phase 1	IG1 & IG2	Session 11	Exercise in chronic pain: Safety guidelines, postural hygiene, and graded exposure to movement. To reduce fear of movement and promote safe physical activity.
Phase 1	IG1 & IG2	Session 12	Attention and efference copy: Influence of attention on pain perception and how the brain automatizes pain. To explain how cognitive focus and automatization perpetuate the pain experience.
Phase 1	IG1 & IG2	Session 13	Neuroplasticity and relapses: The brain’s capacity to change and normalize worse moments during recovery. To foster hope through brain adaptability and normalize clinical setbacks.
Phase 1	IG1 & IG2	Session 14	Delivery of educational leaflet 2, knowledge verification questionnaire, and review of doubts. To consolidate theoretical knowledge and resolve doubts.
Phase 1	IG1 & IG2	Session 15	Resources and available social support: Community programs to improve quality of life and well-being. To integrate the patient into available community health resources.
Phase 1	IG1 & IG2	Session 16	General summary of the key concepts from the previous sessions, Q&A, and motivational closure. To empower the patient for the maintenance phase or independent management.
Phase 2: Maintenance and Behavioral Change (Weeks 9–32)	IG2	Session 17	General review of main concepts: Subjectivity, damage vs. pain, neuroplasticity, and the biopsychosocial approach. To refresh key pain reconceptualization concepts.
Phase 2	IG2	Session 18	Explanatory video on chronic pain and group discussion. To reinforce learning through multimedia and peer discussion.
Phase 2	IG2	Session 19	Confronting erroneous beliefs: Dynamic myths and realities using a color-coded card game. To actively confront and correct remaining erroneous beliefs.
Phase 2	IG2	Session 20	Problem-based learning: Clinical case study of an older woman with chronic pain to find practical solutions. To apply theoretical knowledge to solve real-life scenarios.
Phase 2	IG2	Session 21	Guided debate with practical situations: “What would I do?” dynamic to promote self-efficacy and active decision-making. To improve decision-making and self-efficacy in daily challenges.
Phase 2	IG2	Session 22	Role-playing: Simulating patient-professional conversations to practice empathetic and constructive responses. To practice assertive communication and empathetic understanding.
Phase 2	IG2	Session 23	Guidelines for a healthy diet and cardiac coherence technique (mindful breathing for anxiety reduction). To provide practical somatic tools for anxiety and inflammation reduction.
Phase 2	IG2	Session 24	Guided self-reflection: “What have I changed?”, assessing progress, and closing the program. To assess individual behavioral progress and close the program.

